#### Moxibustion Adherence and Completion

A comprehensive strategy will be used to optimize adherence to home-based moxibustion. Before the intervention, participants will receive standardized training via an instructional video and will be instructed to log details (duration, temperature, and adverse events) as in Multimedia Appendix 4 and media (video or photo) for each session. During the study period, adherence will be promoted through irregular WeChat messages and telephone follow-ups for reminders, supplemented by unannounced random video checks to verify the participants’ procedures. Furthermore, biweekly follow-up visits will be conducted at the research center. These sessions will comprise a face-to-face review of moxibustion logs and video or photo documentation, an assessment of procedural technique and acupoint localization accuracy (Multimedia Appendix 5), and the exchange of used moxa sticks for new supplies.

#### Safety Evaluation

Major adverse cardiovascular and cerebrovascular events, liver function (alanine aminotransferase and aspartate aminotransferase) and kidney function (blood urea nitrogen and creatinine) and moxibustion-related adverse events (burns, blisters, dizziness during moxibustion, ulceration, infection, and local abscesses at the moxibustion site; other discomforts after moxibustion may include dizziness, fatigue, allergies, and loss of appetite) will be recorded in this study. Moreover, adverse events will be monitored through patient self-reports and assessments by health care professionals during the study. Participants will be instructed to immediately report any adverse events to their supervising clinician, who will determine whether further examinations or treatments are necessary and will provide timely interventions. For serious adverse events, the trial will be immediately halted. All adverse reactions, their severity, duration, and any actions taken will be thoroughly documented.

### Data Management and Quality Control

All data related to study participants will be stored and backed up according to trial standards. Case report forms will be uniformly printed after they are designed by the research team, and all trial data for participants will be accurately recorded on these forms. Paper-based data will be retained for at least 3 years. Additionally, an independent data safety monitoring committee (DSMC) will be established before the trial, comprising 3 experts with backgrounds in cardiology, acupuncture, and statistics. The DSMC will hold online meetings every 4 months to oversee trial progress and review data safety and quality. A midterm analysis will be conducted at the halfway point of participant enrollment, and the DSMC will determine whether the trial needs to be terminated early. Personal privacy information (eg, name, age, and phone number) will be anonymized in DSMC reports.

### Statistical Analysis

Data analysis of the primary outcome will be based on the full analysis set constructed by the intention-to-treat principle, whereby patients will remain in their original group regardless of contamination. The per-protocol set will also be analyzed using sensitivity analysis for the primary outcome to evaluate whether contamination affects the direction of the effect. The secondary outcomes will also be compared based on the per-protocol set. The need to impute missing values will be determined by the proportion of and reasons for missing data. If imputation is necessary, appropriate methods, such as the last observation carried forward, the “best-worst-case” scenario, and multiple imputation regression modeling, will be chosen according to the distribution of the missing values.

Potential center effects will be statistically addressed through mixed-effects modeling, notwithstanding standardized central screening and intervention procedures. For primary continuous outcomes, linear mixed-effects models will incorporate the treatment group as a fixed effect and center as a random effect, with center-specific random intercepts accounting for recruitment-related heterogeneity. Secondary outcomes will be analyzed using analogous generalized linear mixed models. The primary analysis will use an intention-to-treat approach. The changes in the primary outcome and other secondary outcomes will be compared by using a linear mixed-effects model with group-by-time point interaction (baseline to week 12). For outcomes measured at multiple time points, a repeated-measures ANOVA will first test for overall group, time, and interaction effects. Upon finding a significant interaction (exact *P* values will be reported), post hoc comparisons will be conducted using a hierarchical adjustment strategy: Benjamini-Hochberg false discovery rate control for the primary outcome across time points and Bonferroni correction for families of secondary outcomes. Sociodemographic and clinical characteristics at baseline will be examined for potential group differences by 2-tailed *t* test or χ^2^ test, with exact *P* values reported. Compliance will be presented using descriptive statistics. The specified significance levels (0.025 for the primary outcome and 0.05 for all other analyses) represent the α thresholds (*P* value cutoffs) for hypothesis testing. All *P* values will be reported per journal style: expressed to two digits (or three if *P*<.01) and as *P*<.001 if below that threshold. Data analysis was conducted with SPSS (version 28.0; IBM Corp).

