### Elimination Criteria

Participants who do not adhere to the study requirements during the trial, and those who do not meet the inclusion criteria after enrollment, will be removed from this study.

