### Dropout Criteria

In this study, the dropout criteria include the following: (1) participants who meet the inclusion criteria but do not complete the trial or who withdraw midway for various reasons; (2) participants who do not follow the prescribed treatment plan or who receive other treatments or medications that interfere with the assessment of efficacy; and (3) participants who are lost to follow-up or die before completing the trial.

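### Per-protocol is the only analysis set the article names for secondary outcomes; the full analysis set should be named as their main set

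*Protocol article*

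**What the plan says.** The protocol article's Statistical Analysis section assigns analysis sets in three consecutive sentences:

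- Primary outcome, main analysis: "Data analysis of the primary outcome will be based on the full analysis set constructed by the intention-to-treat principle".
- Primary outcome, supporting analysis: "The per-protocol set will also be analyzed using sensitivity analysis for the primary outcome".
- Secondary outcomes: "The secondary outcomes will also be compared based on the per-protocol set". This sentence carries no sensitivity label.

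The next paragraph turns to models. It states "Secondary outcomes will be analyzed using analogous generalized linear mixed models", then "The primary analysis will use an intention-to-treat approach", then "The changes in the primary outcome and other secondary outcomes will be compared by using a linear mixed-effects model". None of these sentences names an analysis set for the secondary outcomes.

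Two earlier sections list events after randomisation that take people out. Elimination Criteria removes, among others, "Participants who do not adhere to the study requirements during the trial". Dropout Criteria includes those who withdraw or are lost, and "participants who do not follow the prescribed treatment plan or who receive other treatments or medications that interfere with the assessment of efficacy".

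Under Assessment and Outcomes, the primary outcome is morning systolic pressure. The Holter and heart rate variability indices, the laboratory markers, the constitution score and the MoCA are all secondary.

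**The concern.** For the primary outcome the article uses the usual order for a superiority trial: everyone by assigned group first, then per-protocol as a check. For the secondary outcomes the only set it names is the one that was the check. This is text the article chose to print, so it cannot be put down to detail left to a fuller document.

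The title and objective promise evidence of heart-and-brain protection, and the Discussion presents the MoCA as the measure of cognitive protection. Much of that claim therefore rests on secondary outcomes. A per-protocol comparison conditions on behaviour and events after randomisation, here in a treatment that participants give themselves at home for 12 weeks. If the reasons for exclusion are related to outcome and differ between arms, the groups compared are no longer the groups randomised, and a difference can appear without any treatment effect.

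**Working it through.** **Reading the text.**

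| Outcome | Full analysis set named? | Per-protocol named? | Role of per-protocol |
|---|---|---|---|
| Primary | Yes, expressly | Yes | Sensitivity analysis |
| Secondary | No | Yes | Not stated |

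The intention-to-treat sentence speaks of the primary analysis. That could mean the analysis of the primary outcome, or the main analysis of every outcome. The two sentences on either side of it mention secondary outcomes but describe models, not populations. The main set for secondary outcomes is therefore per-protocol on one reading and unstated on the other. On neither is it expressly the full analysis set.

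**Size of the risk.** The plan gives no figure to reproduce here: it states no exclusion rate and does not define the per-protocol set. I assume that the elimination and dropout criteria mark who leaves it. The only design input is 120 participants allocated 1:1, so 60 per arm.

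Suppose a fraction f of one arm is excluded, their mean outcome is d SD worse than that of those kept, and the other arm loses nobody. The whole-arm mean is then f × d below the kept mean, so the between-group difference shifts by f × d.

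- f = 0.20, d = 0.5: 0.20 × 0.5 = 0.10 SD.
- f = 0.20, d = 1: 0.20 × 1 = 0.20 SD.
- Analysed: 60 × 0.80 = 48 against 60. SE = sqrt(1/48 + 1/60) = sqrt(0.0375) = 0.194 SD.
- Ratio: 0.10/0.194 = 0.52 and 0.20/0.194 = 1.03, so about half to one standard error.
- f = 0.05, same d: 0.025 to 0.05 SD, a quarter of those shifts.

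**Cross-check by simulation, also on assumptions.** There are 60 per arm, no true effect and a normal outcome. The same fraction is excluded from both arms. Exclusion is tied to outcome in one arm (correlation 0.3 or 0.6) and is random in the other. Each setting uses a two-sided t test at 0.05 and 20,000 runs.

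| Excluded | Spurious difference | Type I error |
|---|---|---|
| 5% | 0.03 to 0.06 SD | 5.7% to 6.4% |
| 10% | 0.05 to 0.11 SD | 5.9% to 10.2% |
| 20% | 0.10 to 0.21 SD | 8.1% to 18.7% |

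When exclusion was unrelated to outcome in both arms, the spurious difference was essentially zero and the error rate stayed near 5%.

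**The case against.** The strongest reply is that the article never restricts secondary outcomes to the per-protocol set. The sentence says *also*, and the sentence before it uses the same word for a per-protocol analysis added to a full-set analysis. Read that way, secondary outcomes get both. The intention-to-treat sentence refers to the primary analysis rather than the primary outcome, and sits between two sentences that cover secondary outcomes. A reader might infer that per-protocol is the sole set, but the document does not say so, and I do not claim it. What stands is that a reader cannot tell from the text which set comes first for secondary outcomes, and the only one named is the weaker one.

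A reader might also infer that these comparisons will be biased. The documents do not show that either. Response to treatment is not a listed exclusion criterion, both arms receive the same training and assessment, and participants are described as blinded. Similar selection in both arms would largely cancel. Exclusions linked to blood pressure need not move the MoCA or metabolic markers by the same amount. Against this, removal for non-adherence or other treatment does arise after randomisation, and the Discussion reports that the control acupoint did not significantly lower pressure in preliminary observations. Reasons for added treatment or stopping could therefore plausibly differ by arm. The risk is real, but its size is unknown.

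Two further inferences go too far. Primary and secondary results would not be impossible to read together, because the primary outcome also has a per-protocol analysis. Nor does the protection claim rest on secondary outcomes alone: the Discussion also justifies morning systolic pressure as a predictor of stroke, coronary events and cognitive impairment.

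**Conclusion.** The point holds as a defect in what the article fixes. Per-protocol is the only set named for secondary outcomes, the full analysis set is expressly tied to the primary outcome, and the intention-to-treat sentence does not clearly close the gap. A per-protocol main comparison would expose outcomes that support much of the heart-and-brain claim to selection after randomisation.

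The figure of 0.10 to 0.20 SD, or about half to one standard error, rests on three assumptions: 20% excluded, from one arm only, with outcomes 0.5 to 1 SD worse. At 5% excluded the effect is minor, and with exclusions unrelated to outcome there is none. The change should be made, but the finding is one of risk and unclear wording, not of a bias already shown.

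**What to change.** Replace the sentence on secondary outcomes with: 'Secondary outcomes will be compared in the full analysis set by assigned group, with the per-protocol set as a sensitivity analysis.' Then word the intention-to-treat sentence in the following paragraph so that it expressly covers the main analysis of both primary and secondary outcomes.

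The cost is one new sentence and one aligned sentence, with no change to the sample size or the models. Where later measurements are missing for participants who stopped, the section's existing missing-data provisions apply. The Results section states that no data analysis has been performed; on that statement, the change can still be made before results are known.

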### Sample Size Calculation

The primary efficacy evaluation index for this study is the morning systolic blood pressure measured by 24-hour ambulatory blood pressure monitoring (ABPM). The sample size was estimated based on statistical methods. Preliminary trial data showed that the treatment group had a 7.2 (SD 3.3) mm Hg greater reduction in 24-hour morning systolic blood pressure than the control group. In this study, we apply the superiority design and set the superiority margin (Δ) as 5 mm Hg [22], with a significance level of α equal .025 (1-sided) and a power of β equal .1. The mean value for treatment improvement between the treatment and control groups is set at 7.2 (SD 3.3) mm Hg, with a SD (σ) of 3.3 mmHg, based on the formula for comparing means in a superiority trial [22]:

[figure not shown]

The primary efficacy endpoint of this study was the change in morning systolic blood pressure as measured by 24-hour ABPM. Sample size determination was based on a superiority design for comparing two independent means. The calculation incorporated the following parameters: an expected between-group difference (μ₁–μ₂) of 7.2 mm Hg derived from preliminary data, a common SD (σ) of 3.3 mm Hg, a prespecified superiority margin (Δ) of 5 mm Hg [22], a one-sided α level of 0.025, and 90% statistical power (1–β). These values were applied to the standard sample size formula for superiority trials to ensure adequate power for detecting a clinically meaningful treatment effect.

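### The method for missing primary-outcome values is to be chosen after the missing data are seen, from an unranked list that includes LOCF and a best-worst-case fill

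*Protocol article*

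**What the plan says.** All of this stands in the Statistical Analysis section unless noted.

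- Whether to impute is settled once the data are in: "The need to impute missing values will be determined by the proportion of and reasons for missing data".
- The candidates are "appropriate methods, such as the last observation carried forward", a best-worst-case fill and multiple imputation, and the one used "will be chosen according to the distribution of the missing values". None is named as primary, and none is labelled a sensitivity analysis.
- The rule follows sentences on both primary and secondary outcomes and speaks of missing values in general, so it includes the primary outcome. For that outcome, "Data analysis of the primary outcome will be based on the full analysis set constructed by the intention-to-treat principle".
- Changes are to be "linear mixed-effects model with group-by-time point interaction (baseline to week 12)". The only random effect named is centre. For outcomes with several time points, a repeated-measures ANOVA comes first.
- The Primary Outcome Measure section places the primary assessment at weeks 0 and 12. The Overview under Assessment and Outcomes and Table 1 also schedule ambulatory monitoring at weeks 4 and 24.
- The Sample Size Calculation section uses "an expected between-group difference (μ₁–μ₂) of 7.2 mm Hg derived from preliminary data", an SD of 3.3, a 5 mm Hg margin, one-sided α of 0.025 and 90% power. No dropout rate is stated.

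**The concern.** The three listed methods answer different questions. LOCF supposes that a patient who leaves stays at the last recorded pressure, and it enters that value as if it had been measured at week 12. If only weeks 0 and 12 count for the primary outcome, the last value is the baseline; if the week 4 recording counts, it is week 4. A best-worst-case fill puts extreme values into the gaps to see how far the answer can move. It bounds the result and does not estimate the effect. Multiple imputation can give a valid estimate under missing at random.

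The article treats the three as alternatives and postpones the choice until the missingness is known. The design has only 7.2 − 5 = 2.2 mm Hg to resolve, so a shift of one or two mm Hg from the choice of method is large. Missing week 12 recordings are foreseeable: treatment is given at home for 12 weeks, and the Elimination and Dropout Criteria provide for participants to be removed or to leave.

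**Working it through.** **Inputs from the article:** difference 7.2, SD 3.3, margin 5, one-sided α 0.025, power 90%, 120 patients allocated 1:1.

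**Assumed, because the article does not give them:** share missing at week 12, *d*; share of the final effect present at the last visit, *f*; size of a best-worst fill, *k* SD; change in the control arm.

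**The plan's own figure.** n per arm = 2·3.3²·(1.960 + 1.282)² / 2.2² = 47.3, so 48 per arm and 96 in total. Since 48 / 0.80 = 60, an allowance of 20% would give exactly the stated 120. That 20% is inferred, not stated; it is the reference value below. With all 60 per arm observed, power is 95.5%.

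**A method valid under missing at random.** The expected difference stays 7.2. Counting observed patients only, power is about 93% at 10% missing (54 per arm), 90% at 20% (48) and 86% at 30% (42).

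**LOCF, equal dropout.** Expected difference = 7.2·[(1 − d) + d·f].

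| Missing | Baseline carried (f = 0) | Week 4 carried, half the effect (f = 0.5) |
|---|---|---|
| 10% | 6.48 | 6.84 |
| 20% | 5.76 | 6.48 |
| 30% | 5.04 | 6.12 |

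The difference falls to 5.0 when d = (2.2/7.2)/(1 − f): 30.6% for f = 0 and 61% for f = 0.5. With f of 0.75 or more it never does.

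**Power for LOCF at 20% missing, against the 5 mm Hg margin.**

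- Ignoring the extra spread from filled values, SE = 3.3·√(2/60) = 0.6025. For f = 0, 0.76/0.6025 − 1.96 = −0.70, so 24%. For f = 0.5, 1.48/0.6025 − 1.96 = 0.50, so 69%.
- Counting the mixture of filled and observed values, with no change in the control arm and f = 0, the treated variance is 0.8·3.3² + 0.8·0.2·7.2² = 17.01 and the control variance is 0.8·3.3² = 8.71. SE = √(25.72/60) = 0.655, so power is 21%. The same step gives 65% for f = 0.5.
- If the control arm also falls by 2 mm Hg (assumed), simulation with 20,000 replicates gives about 19% for f = 0 and 62% for f = 0.5.

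**LOCF, unequal dropout.** Suppose both arms fall by 5 mm Hg apart from the treatment effect, so the treated fall is 12.2, and baseline is carried forward.

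- 25% missing on treatment, 15% on control: 0.75·12.2 − 0.85·5 = 4.90.
- 10% on treatment, 30% on control: 0.90·12.2 − 0.70·5 = 7.48, above the true 7.2.

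**Best-worst fill, *k* SD from the own-arm mean in opposite directions.** Shift = 2·k·3.3·d. At 20% missing this is 1.32 for k = 1 and 2.64 for k = 2.

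- Adverse direction: 5.88 or 4.56. The 2 SD fill reaches 5.0 at 2.2/13.2 = 16.7% missing, the 1 SD fill at 2.2/6.6 = 33%.
- Favourable direction: 8.52 or 9.84. A true difference of 5.0, exactly at the margin, would appear as 6.32 or 7.64.

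**The case against.** Several points on the other side stand.

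- Imputation is conditional, the list is given as examples, and multiple imputation, which is acceptable, is on it.
- The Blinding section says statisticians do not know the allocation. That limits selection of a method by its result. It does not make LOCF or a best-worst fill a valid primary estimate, and it does not fix the method.
- Every size rests on values that the article does not state. The 19–24% power also needs every missing patient to contribute only a baseline value, although a week 4 recording is scheduled, so it is a bound and not an expectation.
- The power figures assume a test against 5 mm Hg. The margin appears only in the Sample Size Calculation section. Against zero, a difference of 5.76 with an SE of about 0.73 (the case in which controls also fall by 2) gives z of about 7.9, and attenuation would cost essentially no power.
- A protocol may leave details of imputation to a separate analysis plan. Here, though, the article does state a rule, and it is that rule which is open to objection.

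Three stronger readings are tempting and are not supported. A reader might infer that LOCF would drag a true 7.2 down to the margin. Under equal dropout that takes about 31% missing even with baseline carried forward, and of the own-arm fills shown only the assumed 2 SD adverse one gets there at 20%. A reader might infer that the error runs only downward, but favourable fills and unequal dropout can inflate the estimate. A reader might also infer that the planned mixed model already uses every ambulatory recording, so that imputation is redundant. The article does not establish this: the primary outcome is tied to weeks 0 and 12, no within-patient term is named, and the repeated-measures ANOVA placed first in its usual form needs complete cases.

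**Conclusion.** The point holds as a badly fixed rule. The article lets the handling of missing primary-outcome values be settled after the missingness is seen, and two of its three unranked options should not produce the primary estimate. At an assumed 20% missing in both arms, the choice alone spans roughly 4.6 to 9.8 mm Hg around a true 7.2, with fills of up to 2 SD from the own-arm mean. LOCF under equal dropout takes up the narrower part from 5.76 up to 7.2. Less missing data narrows all of these ranges. The main risk is an undetermined method that can move the result either way relative to the margin, not attenuation as such. Blinding and the presence of multiple imputation on the list reduce the risk without removing it. This should be corrected before the analysis; it does not invalidate the design.

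**What to change.** Before unblinding, amend the Statistical Analysis section to name one primary approach valid under missing at random, whatever proportion turns out to be missing. Either of these would serve:

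- the linear mixed model on all observed ambulatory recordings at weeks 0, 4 and 12, with the within-patient correlation and the visits used written out, the week 12 contrast named as the primary estimate, and no complete-case repeated-measures ANOVA as a preceding step for it; or
- multiple imputation, with the imputation model stated.

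Label best-worst-case, and LOCF if it is kept, as sensitivity analyses only, and state the fill values and which visit is carried forward. A multiple imputation with delta adjustment would be a useful optional sensitivity analysis.

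The article reports that data collection ended in February 2025 and that no analysis has been done. The missingness pattern may therefore already be visible, but the method can still be fixed before allocation is revealed. The cost is a wording change and one extra sensitivity run; no new data are needed.

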**Methods:**

This study is a multicenter, randomized controlled trial. A total of 120 patients with mild to moderate hypertension and phlegm-dampness constitution will be recruited and randomly assigned in a 1:1 ratio to the treatment group (acupoint: Zusanli, ST36) or the control group (acupoint: Xuanzhong, GB39). All patients will receive 12 weeks of treatment and a 12-week follow-up period. The primary outcome measure is the change in morning systolic blood pressure from baseline to week 12. The secondary outcome measures include blood pressure–related indicators (morning diastolic blood pressure, average systolic blood pressure, average diastolic blood pressure, nighttime systolic blood pressure, nighttime diastolic blood pressure, and blood pressure circadian rhythm) and short-term blood pressure variability coefficient, all of which will be measured by 24-hour ambulatory blood pressure monitoring. Additionally, cardiac-related indicators measured by 24-hour Holter monitoring, metabolic disorder-related indicators, liver and kidney function indicators, transformed scores of the traditional Chinese medicine phlegm-dampness constitution scale, and the Montreal Cognitive Assessment will also be evaluated.

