## Methods

### Ethical Considerations

This study protocol was approved by the Ethics Committee of the Shanghai Tongji University-affiliated Oriental Hospital (2023 research review: 145), the Shanghai University of Traditional Chinese Medicine-affiliated Longhua Hospital (2024LCSY161), and the Shanghai Acupuncture and Meridian Research Institute (2023-169). Written informed consent was obtained from all participants prior to the study and data publication. All study-related examinations and treatments will be provided to participants free of charge. No additional compensation will be offered. The study was registered on July 5, 2024, with the Chinese Clinical Trial Registry (ChiCTR2400086582). All participants will be provided with detailed study information and must provide written informed consent prior to enrollment. The trial results will be submitted for publication in a peer-reviewed journal. Neither patients nor the public were involved in the study's design, conduct, reporting, or dissemination plans.

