### Case Selection

Participants in this trial are outpatients receiving treatment between June 2023 and February 2025 at the Oriental Hospital affiliated with Tongji University, Longhua Hospital affiliated with Shanghai University of Traditional Chinese Medicine, and the Shanghai Research Institute of Acupuncture and Meridian. All patients are recruited and screened based on the inclusion and exclusion criteria outlined in the study.

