#### Primary Outcome Measure

In this study, the primary outcome measure is the morning systolic blood pressure, which will be measured by 24-hour ABPM (assessment at weeks 0 and 12).

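### The primary analysis of morning systolic pressure does not adjust for its baseline value, which costs precision but not validity

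*Protocol article*

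**What the plan says.** The abstract of the protocol article states: "The primary outcome measure is the change in morning systolic blood pressure from baseline to week 12". The Primary Outcome Measure section names "the morning systolic blood pressure, which will be measured by 24-hour ABPM (assessment at weeks 0 and 12", so a baseline reading is scheduled for every participant.

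The Statistical Analysis section describes the primary model in two places:

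- On centre effects, "linear mixed-effects models will incorporate the treatment group as a fixed effect and center as a random effect". The random part is described as one intercept per site, meant to absorb differences in recruitment.
- A few sentences later, changes in the primary and other secondary outcomes "will be compared by using a linear mixed-effects model with group-by-time point interaction (baseline to week 12".

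It adds that outcomes with several visits go first through a repeated-measures ANOVA. None of these sentences names baseline morning systolic pressure as a covariate, a patient-level random effect or a within-patient covariance structure. Case Selection lists three sites: "Oriental Hospital affiliated with Tongji University, Longhua Hospital affiliated with Shanghai University of Traditional Chinese Medicine, and the Shanghai Research Institute of Acupuncture and Meridian".

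**The concern.** With two time points, a group-by-time interaction is the between-arm difference in mean change. It subtracts the whole of the baseline value, whereas regression on baseline subtracts only the fraction that predicts the week-12 value. When the correlation between visits is below 1, full subtraction adds noise. It also passes chance baseline imbalance into the estimate: the change-score and adjusted estimates differ by (1 − ρ) times the observed baseline difference between arms.

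Precision matters here because the Sample Size Calculation section tests against a 5 mm Hg margin. Of the expected 7.2 mm Hg, only 7.2 − 5 = 2.2 mm Hg drives the power.

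A secondary matter is that centre is the only random effect named. An analyst who stacked both visits and fitted only that term would treat two readings on one patient as independent.

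**Working it through.** **Inputs from the article.** 120 patients, 1:1, so 60 per arm; expected difference 7.2 mm Hg; margin 5 mm Hg; SD 3.3 mm Hg; one-sided alpha 0.025; power 90%.

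**Assumptions.** 3.3 mm Hg is the SD of the change; variances are equal at the two visits; there is no dropout. The baseline to week-12 correlation ρ is not in the article, so a range is shown.

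**The plan's own figure.** n per arm = 2 × (1.960 + 1.282)² × 3.3² / 2.2² = 47.3, rounded up to 48, or 96 in total. The stated 120 equals 96 / 0.80, which would fit a 20% dropout allowance that the article does not state. The present point does not depend on this, and 120 is not called wrong here.

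**Change score at 60 per arm.** SE = 3.3 × √(2/60) = 0.602. Power = Φ(2.2/0.602 − 1.960) = 95.5%.

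**Baseline-adjusted.** With visit variance σ², the change has variance 2σ²(1 − ρ) and the adjusted outcome σ²(1 − ρ²). The ratio is (1 + ρ)/2. Power = Φ(2.2/SE − 1.960).

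| ρ (assumed) | Variance ratio | Variance saved | SE | Power, 60 per arm | Power from a 90% start |
|---|---|---|---|---|---|
| 0.3 | 0.65 | 35% | 0.486 | 99.5% | 98% |
| 0.5 | 0.75 | 25% | 0.522 | 98.8% | 96% |
| 0.7 | 0.85 | 15% | 0.555 | 97.7% | 94% |

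The last column uses Φ(3.242/√ratio − 1.960), where 3.242 = 1.960 + 1.282. At ρ = 0.8 the saving is 10% and power at 60 per arm is 97.1%.

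**Literal fit to both visits with only a centre intercept.** The model's interaction variance is 4σ²/n, while the true variance is 4σ²(1 − ρ)/n. The model SE is therefore too large by k = 1/√(1 − ρ). The estimate's real spread does not change, so power is Φ(2.2/0.602 − 1.960k).

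| ρ (assumed) | k | Model SE | Actual one-sided alpha | Power, 60 per arm |
|---|---|---|---|---|
| 0.3 | 1.20 | 0.720 | 0.0096 | 90.5% |
| 0.5 | 1.41 | 0.852 | 0.0028 | 81.0% |
| 0.7 | 1.83 | 1.100 | 0.0002 | 52.9% |

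A simulation (300 runs per ρ) gave mean model SEs of 0.714, 0.847 and 1.092 against empirical SEs of 0.596, 0.635 and 0.642, in line with the formula within simulation error.

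**Centre as random or fixed.** A simulation used three centres of 40, patients randomised individually, centre SD from 0 to 3 mm Hg and 400 runs per setting. The treatment SE was 0.601–0.603 with random centre and 0.604–0.607 with fixed centre. Empirical SEs agreed to within 0.001.

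**The case against.** The strongest reply is that the plan is already valid. Baseline enters through the change or as a time point, randomisation makes the contrast unbiased on average, and power at 60 per arm is already 95.5% on the plan's own inputs. On that footing the gain is only about 2 to 4 percentage points. This stands as a limit on the size of the point. It does not remove the point, because the gain uses data already scheduled, and it is larger if the sample falls towards the 96 that the inputs require.

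The reply on the patient term is also good. The sentence naming centre explains how centre effects are handled and need not list every term. Fitted to one change per patient, as the abstract's definition allows, the model needs no patient term. If both visits are outcomes, the repeated-measures ANOVA named in the same section shows that the data are regarded as repeated. An article may leave the covariance structure to a fuller plan. A reader might infer that the primary standard error will be wrong, but the text does not establish that; it is one literal reading.

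A reader might also infer that three centres are too few for a random effect and so distort the treatment standard error. The centre variance does rest on 2 degrees of freedom and can be estimated at zero. Patients are randomised individually, however, so centre largely cancels from the treatment contrast, and the simulated standard errors are almost the same either way.

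**Conclusion.** The point holds as one of efficiency. The primary analysis, as written, is a change-score comparison without baseline adjustment. Adjusting would lower the variance of the treatment effect by 35%, 25% or 15% at correlations of 0.3, 0.5 or 0.7. These sizes rest on the assumed correlations and on equal variances at the two visits; the power figures also need 3.3 mm Hg to be the SD of the change and no dropout.

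Three stronger conclusions are not supported. Baseline is not ignored outright, and leaving it out as a covariate does not bias the estimate on average. The number of centres does not make the treatment standard error wrong. The absence of a named patient term does not show that the analysis will be wrong; if the literal model were fitted, the error would be conservative, costing power without raising the false-positive rate. It is still worth making that term explicit, because the possible loss of power is larger than the gain from baseline adjustment.

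**What to change.** State one primary model: week-12 morning systolic pressure (or its change from baseline) regressed on group, baseline morning systolic pressure and centre, with the group coefficient as the treatment effect.

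If several visits are modelled together, use one longitudinal model with baseline as a covariate or with a baseline mean common to both arms, and an unstructured within-patient covariance. Take the week-12 contrast as the primary result.

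Enter centre as a fixed factor for tidiness with three sites, and do not present this as correcting a standard error.

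The cost is analysis wording and three model degrees of freedom (one for baseline, two for centre), with no new data. The article's Results section says that no analysis has yet been done, so the change can be recorded and dated before any comparison by arm.
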